### Randomization and allocation

2.4

The patients diagnosed by orthopedists were screened for eligibility based on clinical inclusion criteria. The medical records of those who met the criteria were then forwarded to surgical pharmacists. Patients were randomly assigned to standard care or pharmacist-involved care (1:1 ratio) by team members not involved in clinical pharmacy services, based on whether they received intervention from surgical pharmacists. A dynamic stratified block group randomization method was used to randomly group participants, stratified by sex and age of participants, using R package blockrand (R version 4.0.3).

### Standard care

2.5

Orthopedists conducted routine evaluations and therapy for all enrolled patients with OF. This process included diagnosing the condition, conducting ward rounds, prescribing medications, performing surgical interventions when necessary, and documenting medical records. Moreover, the orthopedists provided a brief overview of osteoporosis and key instructions to patients with OF. However, surgical pharmacists were not included in discussions related to osteoporosis during this process.

### Surgical pharmacist intervention pathway

2.6

The goals of pharmaceutical care involved both orthopedists and patients with osteoporotic fractures. On the one hand, surgical pharmacists provided prescription reviews and consultations with physicians on treatment options for osteoporosis. On the other hand, pharmaceutical care for patients consisted of explaining the importance of diagnosing and treating osteoporosis, providing guidance on the fall risks, and outlining the main precaution related to the use of anti-osteoporotic drugs.

Patients allocated to the intervention group received pharmacist-involved care to identify the effects of pharmaceutical services in OF treatment. On the basis of the standard care, surgical pharmacists, dressed in standard and appropriate professional attire, conducted bedside pharmaceutical consultations individually at three distinct stages: on the first day of admission; within 1 week post-surgery or once the condition is stable; and on the day of discharge. This interaction typically spans a duration of 10–20 min.

#### Day 1 of admission

2.6.1

A drug reorganization form will be completed to collect medication history, drug allergies, and current medication use, as recorded by the surgical pharmacist through pharmaceutical diagnosis. The bone mineral density (BMD) measurement and exact therapeutic plans are formulated by orthopedists. Consultative reviews are further established by surgical pharmacists, focusing on: (1) the usage and dosage of therapeutic drugs; (2) soluble media; (3) drug contraindication; (4) risks of adverse drug reactions (ADRs); and (5) collaborative drug treatment for chronic disease, including diabetes, hypertension, and hyperlipidemia. Surgical pharmacists will send a new medicine/deprescribe or a change based on the consultative review to orthopedists if indicated. Otherwise, it is necessary for surgical pharmacists to communicate with orthopedists and nurses for medication errors, adjustment in current medicines, and provide medical consultation.

#### Postoperative or stable condition within 1 week

2.6.2

First, the surgical pharmacist uses the Fracture Risk Assessment Tool (FRAX) to evaluate the risk of fracture. Second, the individualized therapeutic options for osteoporosis are formulated under the guidance of the Clinical Pathway of anti-osteoporotic drugs of patients with osteoporosis formulated by surgical pharmacists and orthopedists. Third, all participants will be educated by surgical pharmacists, including the usage of anti-osteoporotic drugs, the importance of persisting with osteoporosis medication, maintaining physical activity, and prevention of falling. Furthermore, patients will be provided a brochure on preventing fractures to enhance the consciousness of osteoporotic fractures.

#### One day of discharge

2.6.3

The current drug list, along with guidance for self-care, will be conducted. All participants will receive an educational brochure explaining the customized treatment of osteoporotic fracture, such as dosage, precautions for medicine taking, ADRs monitoring, and specific follow-up time.

#### After discharge

2.6.4

We evaluate outcomes of pharmacology interventions during 2 years following the start of discharges, using telephone interviews, clinic visits, and pharmacy practice in e-hospitals. Follow-up time points are set at 1 week, 1 month, 3 months, and then every 3 months thereafter until 24 months post-discharge.

### Regular follow-up and engagement

2.7

Participants who did not take the medication as scheduled beyond 8 weeks of the expected follow-up period, as well as those who no longer wish to participate in the study, were discontinued from the study.

To address the potential for missing data due to the high dropout rate in the elderly population, we will incorporate an intention-to-treat (ITT) analysis approach. ITT analysis will include all randomized participants in the analysis according to their assigned group, regardless of whether they completed the follow-up or not, which may minimize the bias introduced by missing data and provide a conservative estimate of the treatment of the treatment effect (6).

Participants will be followed up at 1 week, 1 month, 3 months, and then every 3 months thereafter for a total of 24 months. This frequent and structured follow-up schedule is designed to enhance participant retention and ensure comprehensive data collection.

Multiple follow-up methods, including telephone interviews, pharmaceutical clinic visits, and pharmacy practice in e-hospitals, will be used to accommodate different preferences and accessibility of elderly patients.

Trained pharmacists will conduct telephone interviews to gather detailed information on medication use, adverse reactions, falls, and fracture events. Face-to-face consultations at the pharmaceutical clinic will provide personalized medication education and counseling, addressing patient questions and offering the necessary support. For patients unable to visit the clinic, real-time pharmacy practice in e-hospitals via video conferencing or instant messaging will ensure timely information and support.

To ensure comprehensive coverage and maintain data quality, all research staff involved in data collection, including pharmacists and clinic personnel, underwent comprehensive training on the study protocol, data collection methods, and the use of standardized tools. Additionally, we involved family members or caregivers in the follow-up process to provide accurate information on participants’ conditions and medication adherence, ensuring complete and reliable data.

To encourage participant retention, educational materials and personalized support were provided during each follow-up session.

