#### Primary results

2.8.1

The primary outcome, assessed within 2 years post-discharge, is defined as the treatment rates of anti-osteoporotic drugs among patients receiving pharmacist-led interventions compared to those on conventional treatment. The treatment rates are calculated as the ratio of patients who still use anti-osteoporotic drugs to the total number of enrolled participants.

Ongoing treatment is defined as the uninterrupted use of anti-osteoporotic medications, where any treatment interruption lasting more than 60 days is considered as discontinuation (21). According to previous studies, interruptions in osteoporosis treatment exceeding this duration are associated with an increased fracture risk and reduced treatment efficacy (7, 22).

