### Statistical analysis

2.11

The statistical analysis will be along with the intention-to-treat (ITT) principles. The ITT population will include patients who meet the criteria, are randomized, and take at least one dose of drugs after being enrolled (Figures 2, 3).

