**Figure 3 fig3:**
[figure not shown]
Surgical pharmacist-led intervention pathway of this study.

All counting data will be analyzed using the Statistics Package for the Social Science (SPSS) program, version 23.0. Continuous variables are expressed as mean or median (quarterly distance) with standard deviation (mean ± SD), and categorical variables are expressed as frequencies or percentages. The *t*-test will be used to compare continuous data that satisfies normal distribution or the Willcoxon test will be performed for the skewed distribution data. The chi-squared test or Fisher’s exact test will be used to assess the comparison of categorical data in different groups.

For outcomes such as continued treatment rates of anti-osteoporotic drugs, Kaplan–Meier curves will be used to characterize how the probability of an endpoint event changes with survival time, and comparisons between survival curves will be carried out using log-rank tests. We used the Cox proportional hazards model to estimate the hazard ratios and 95% confidence intervals. Missing observations were accounted for using the predictive mean matching (PMM) method. If the missing data are numerical, it will be filled by predictive mean matching; meanwhile, if the missing data are non-numerical, logistic regression and discriminant functions will be used to fill it. The *p*-value threshold is 0.05 (*p* < 0.05), and a p-value below this threshold indicates that the difference is statistically significant.

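### Not taking the drug beyond 8 weeks removes a participant from the study, although staying on the drug is the primary outcome, and the protocol does not say how those removed are scored

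*Protocol article*

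**What the plan says.** Section 2.7 (Regular follow-up and engagement) names two groups that leave the trial: those who no longer wish to take part, and "Participants who did not take the medication as scheduled beyond 8 weeks of the expected follow-up period". Both "were discontinued from the study", so the consequence is loss from the study, not a change of treatment status. Non-use of the drug is not among the withdrawal criteria in section 2.3.

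Section 2.8.1 (Primary results) defines the primary outcome as "the ratio of patients who still use anti-osteoporotic drugs to the total number of enrolled participants", and adds that "any treatment interruption lasting more than 60 days is considered as discontinuation".

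On analysis, the next paragraph of 2.7 turns to missing data from dropout and says "ITT analysis will include all randomized participants in the analysis according to their assigned group, regardless of whether they completed the follow-up or not". Section 2.11 (Statistical analysis) analyses continued treatment by Kaplan–Meier curves, log-rank tests and a Cox model. It also says "Missing observations were accounted for using the predictive mean matching (PMM) method", with logistic regression or discriminant functions for non-numerical values. No section says that a participant removed under the 8-week rule counts as a failure, or is still followed.

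**The concern.** In a trial of persistence with medication, stopping the drug is the event to be counted. A rule that ends study participation because the drug was not taken selects participants out on the outcome. Two things are then at stake.

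The first is the primary comparison. If those removed are handled as ordinary dropouts, by imputation from participants still observed or by censoring in the survival analysis, the missingness is informative and persistence is overstated. The bias need not be equal in the two arms.

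The second is everything measured after removal. Refractures at 1 and 2 years, falls, DXA at 1 and 2 years, and treatment satisfaction are no longer collected in the patients who stopped treatment. Keeping these people in an intention-to-treat analysis set does not supply data that were never gathered.

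**Working it through.** **Timing.** Removal trigger (2.7): 8 weeks = 8 × 7 = 56 days. Failure definition (2.8.1): more than 60 days. Read as days off drug, any spell that reaches the failure definition passed the removal trigger at least 60 − 56 = 4 days earlier.

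**The plan's own figure.** Inputs from section 2.10: 50% versus 30%, two-sided α = 0.05, power 80%, dropout 20%. With the unpooled normal formula,

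n = (1.960 + 0.842)² × (0.50 × 0.50 + 0.30 × 0.70) / (0.50 − 0.30)² = 90.26, rounded up to 91 per group.

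Then 91 / 0.80 = 113.75, rounded up to 114 per group, 228 in total. The stated 91, 114 and 228 are reproduced and are not in question.

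**How many participants the rule could reach.** With 114 per arm at the planned rates:

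- intervention non-continuers: 114 × 0.50 = 57
- control non-continuers: 114 × 0.70 = 79.8
- together: 136.8 / 228 = 60%, three times the 20% dropout allowance.

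The percentages are the same if 91 per arm is used.

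**Primary rate under two ways of scoring those removed.**

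(a) Removed participants stay in the all-enrolled denominator and count as not on treatment. The rate is p whatever share is removed: 50% versus 30%. There is no bias.

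(b) A fraction f of non-continuers is treated as missing and like those observed. The apparent rate is p / (p + (1 − p)(1 − f)). The documents give no value for f, so a range is shown, equal in both arms:

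| f | Share of all participants missing (0.60 × f) | Intervention | Control |
|---|---|---|---|
| 0.25 | 15% | 57.1% | 36.4% |
| 0.50 | 30% | 66.7% | 46.2% |
| 0.75 | 45% | 80.0% | 63.2% |
| 1.00 | 60% | 100% | 100% |

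For f = 0.50: 0.50 / (0.50 + 0.25) = 0.667 and 0.30 / (0.30 + 0.35) = 0.462. The table concerns the rate. Censoring in a Kaplan–Meier analysis would give other figures, but persistence would again be overstated.

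The document does not choose between (a) and (b). The definition in 2.8.1 permits (a); the methods in 2.11 permit (b).

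**The case against.** The strongest reply is that the primary measure already protects itself. Its denominator is everyone enrolled, so a removed non-user stays below the line, is absent above it, and is counted as a failure. Section 2.7 also keeps all randomized participants in the analysis "regardless of whether they completed the follow-up or not", and event and censoring rules are commonly left to an SAP. This stands in part: the inflated rates under (b) are conditional, and nothing in the article says that removed participants will be censored or imputed. But nothing says that they will be scored as failures either. No SAP can recover follow-up that the protocol has ended.

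Three stronger readings are tempting and are not supported:

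- **That every failure is lost before it can be recorded.** The 8-week wording is loose and may describe a window around an expected visit. After month 3 the visits are three months apart (2.6.4, 2.7), so some lapses will be found only after day 60 and could be recorded.
- **That lapses will be detected differently by arm.** Section 2.7 gives one schedule for participants, while the Discussion lists follow-ups as part of the intervention. Detection may differ. If 60% and 40% of non-continuers were lost with a true rate of 30% in both arms, the apparent rates would be 0.30 / (0.30 + 0.28) = 52% and 0.30 / (0.30 + 0.42) = 42%, but that split has no source in the documents.
- **That the contrast disappears.** The 100% versus 100% row needs every non-continuer to be lost and treated as missing.

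Never-starters are a related but separate matter: section 2.11 limits its ITT population to those who "take at least one dose of drugs after being enrolled", which conflicts with section 2.7.

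**Conclusion.** The concern holds in this form: the protocol removes participants from the study for the behaviour that its primary outcome measures, at a nominally shorter duration (56 against 60 days), and does not state how they are scored. The rule could reach up to 50% of the intervention arm and 70% of the control arm at the planned rates.

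The effect on the primary rate ranges from none to serious. It is none if those removed are counted as not on treatment over all enrolled. If half of the non-continuers were treated as missing and like those observed, 50% versus 30% would appear as 67% versus 46%. That figure rests on an assumed f, equal in both arms, and on departing from the denominator in section 2.8.1.

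The loss of later refracture, fall, BMD and satisfaction data does not depend on that choice. It follows from the removal itself.

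**What to change.** Reconcile sections 2.7, 2.8.1 and 2.11, and align 2.3 with them:

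- Remove non-use of medication as a ground for leaving the study. Withdrawal of consent is unaffected.
- State that anyone whose interruption exceeds the protocol's own 60-day limit is scored as not on treatment. In the Kaplan–Meier and Cox analyses this is an event, and it is not censored or imputed for this reason.
- State that these participants stay in the scheduled follow-up to 24 months for all outcomes.
- For anyone already removed under the rule, score the lapse as the event and collect later outcomes only as far as their consent allows.

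The sample size of 228 does not change. The cost is a protocol amendment, continued contacts on the existing schedule with participants who have stopped the drug, and a check of consent for those already removed. The persistence estimate may be lower than it would be if these participants were treated as missing.

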### Sample size

2.10

The sample size estimation was determined by measuring a clinically significant difference in the primary outcome—continued treatment rates of anti-osteoporotic drugs between the intervention and control groups. To achieve a statistical power of 80% (β = 0.20) with a significance level of α = 0.05 (two-sided), we conducted a sample size calculation using the following assumptions.

Based on previous studies, we assumed a continued treatment rate of 50% in the intervention group (P1) and 30% in the control group (P2) (1, 7). Considering the potential high dropout rate among the older adult population, we accounted for a 20% dropout rate over the 2-year follow-up period. The calculation resulted in a required sample size of 91 participants per group. Considering a 20% dropout rate, we adjusted the sample size to 114 participants per group, resulting in a total sample size of 228 participants. The sample size is calculated by PASS15.0 software, and the calculation equation is shown in Figure 1.

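### Section 2.7 credits intention-to-treat with limiting missing-data bias and giving a conservative estimate; that holds only in special cases, and the effect can instead be overstated

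*Protocol article*

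**What the plan says.** Section 2.7 (Regular follow-up and engagement) expects many elderly participants to drop out and brings in ITT to deal with the resulting missing data. It says that analysing all randomized participants in their assigned group is an approach "which may minimize the bias introduced by missing data and provide a conservative estimate of the treatment of the treatment effect".

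Four other statements bear on this:

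- Section 2.7 discontinues from the study participants who fail to take their medication beyond 8 weeks, as well as those who no longer wish to take part.
- Section 2.8.1 defines the primary outcome as "the ratio of patients who still use anti-osteoporotic drugs to the total number of enrolled participants", and treats an interruption of more than 60 days as discontinuation of treatment.
- Section 2.11 says: "Missing observations were accounted for using the predictive mean matching (PMM) method". It then assigns logistic regression and discriminant functions to non-numerical data. For continued treatment it names Kaplan–Meier curves, log-rank tests and a Cox model.
- Section 2.10 plans for dropout: "we accounted for a 20% dropout rate over the 2-year follow-up period". No split by arm is given.

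A related point needs reconciling: section 2.7 puts all randomized participants in the ITT set, whereas section 2.11 also requires at least one dose.

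**The concern.** ITT is a rule about the analysis set. A patient whose drug status at 24 months is unknown stays in the set, but the status still has to come from a further rule or assumption. Any bias comes from that assumption and from who drops out. Calling the result conservative tells readers that errors run against the intervention, and nothing in section 2.7 secures this.

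The issue is sharper here because one route out of the study is not taking the drug, and being on the drug is the outcome. Patients who leave that way are probably off drug more often than those who stay, so filling in their status from those who stay would overstate drug use. With 20% dropout planned and a 20-point effect sought, the assumption about dropouts can move the result materially.

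**Working it through.** **The plan's own figures.** Inputs from section 2.10: 50% vs 30%, two-sided α = 0.05, power 80%, dropout 20%.

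n = (1.960 + 0.842)² × (0.5×0.5 + 0.3×0.7) / 0.20² = 90.26, rounded up to 91 per group. Then 91/0.8 = 113.75, rounded up to 114. Both stated figures reproduce; the sample size is not at fault.

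**Case 1: dropouts imputed from observed patients (section 2.11).** Let p be the true on-drug rate in an arm, d its dropout and r the dropouts' on-drug rate relative to completers. The completers' rate c satisfies p = c(1−d) + c·r·d, so c = p/[(1−d) + d·r]. I assume that imputation gives an arm's dropouts the same rate as its completers, so the estimate is c.

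Equal 20% dropout, true 50% vs 30%:

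- r = 0 (all dropouts off drug): 0.5/0.8 = 62.5% vs 0.3/0.8 = 37.5%, **25 points**.
- r = 0.5: 0.5/0.9 = 55.6% vs 0.3/0.9 = 33.3%, **22.2 points**.

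No difference in dropout between arms is needed. With unequal dropout and r = 0:

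- 10% intervention, 30% control: 0.5/0.9 − 0.3/0.7 = 12.7 points.
- 30% intervention, 10% control: 0.5/0.7 − 0.3/0.9 = 38.1 points.

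**Case 2: dropouts counted as off drug in the all-enrolled ratio (a reading of section 2.8.1).** If leaving is unrelated to drug use, the estimated rate is p(1−d). The splits below are assumptions that average the planned 20%. True rates are 50% vs 30%.

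| Dropout, intervention / control | Estimated rates | Difference |
|---|---|---|
| 20% / 20% | 40.0% vs 24.0% | 16 points |
| 15% / 25% | 42.5% vs 22.5% | 20 points |
| 10% / 30% | 45.0% vs 21.0% | 24 points |
| 25% / 15% | 37.5% vs 25.5% | 12 points |
| 30% / 10% | 35.0% vs 27.0% | 8 points |

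With no true effect (40% in both arms) and 10% / 30% dropout: 0.40×0.9 = 36% vs 0.40×0.7 = 28%, a false 8 points. For a two-sided chi-squared comparison with 114 per arm, the standard error is √(2×0.32×0.68/114) = 0.0618 under the pooled null and √[(0.36×0.64 + 0.28×0.72)/114] = 0.0616 otherwise. The chance of rejecting in favour of the intervention is Φ[(0.08 − 1.96×0.0618)/0.0616] = 25.2%, and 25.3% counting both directions. It is 18.5% if the common rate is 30% and 33.7% if it is 50%. With 20% / 20% dropout it is 5.0%.

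**The case against.** The strongest defence is that the sentence is hedged with the word may and gives a rationale, not an analysis rule. Section 2.11 adds imputation and section 2.7 lists retention measures. All of that stands. A reader might infer that ITT is the trial's only missing-data measure or that the estimate is never conservative; neither is right. Equal dropout counted as off drug gives 16 points. Imputation with less dropout in the intervention arm also errs on the low side (12.7 points above).

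Four other stronger readings are not supported:

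- **That dropout will differ by arm.** Section 2.7 says "To encourage participant retention, educational materials and personalized support were provided during each follow-up session", without limiting this to one arm. The Discussion lists up to 10 follow-ups as part of the pharmacist-led intervention, so unequal dropout is plausible, but no document establishes it.
- **That counting dropouts as off drug is a stated rule.** Section 2.8.1 gives a numerator and a denominator and does not say how a dropout is scored. Patients removed for not taking the drug would be scored broadly correctly as off drug, so the Case 2 inflation applies only to other dropouts, whose share is unknown.
- **That the trial's error rate would be 25%.** That figure is for a chi-squared comparison of rates. Section 2.11 lists chi-squared for categorical data generally, but names log-rank and Cox for continued treatment, and no error rate was computed for those.
- **That no dropout rule could be conservative.** Scoring missing intervention patients as off drug and missing controls as on drug would be conservative at any split.

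Finally, sensitivity analyses are commonly left to an SAP, which is not shown. Their absence from this article is not the fault alleged; the fault is the property that the article claims for ITT.

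**Conclusion.** The point holds. Section 2.7 gives ITT a property that it lacks, and the word may does not repair this, because conservatism depends on the dropout split and the scoring rule, not on ITT.

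The firmest illustration is Case 1: 20 points become 25 if all dropouts are off drug, or about 22 if they are on drug half as often as completers, with equal 20% dropout. It assumes that section 2.11's imputation is applied to drug status and reproduces the observed rate in each arm. Predictors that capture drug status at the time of leaving would reduce the bias. The 8-week rule in section 2.7 makes the direction credible; its size depends on how many dropouts leave by that route, which is not given.

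Case 2 (20 points to 24, or a false 8 points) is conditional on an inferred scoring rule, an assumed 10% vs 30% dropout and dropout unrelated to drug use. Other splits hide an effect.

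**What to change.** 1. In section 2.7, delete the clause about minimising bias and giving a conservative estimate. State that ITT defines the analysed set and the arm, and nothing about unseen outcomes.
2. Score patients discontinued for not taking the drug by their known drug status instead of imputing it. The 8-week removal rule (56 days) and the interruption of more than 60 days in section 2.8.1 must be reconciled so that this status is defined; which period applies is for the sponsor to settle.
3. Add one tipping-point analysis of the 24-month treatment rate. Vary the share of the remaining dropouts assumed on drug from 0 to 100%, separately in each arm, and report the combinations at which the conclusion changes.
4. Report dropout by arm and reason, so that readers can judge which part of that grid is plausible.

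The cost is a few lines of wording and one extra table from data already held. The downside is that the result may have to be reported as less certain.
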